## Abstract

**Background:**

Shift work is considered a risk factor for a number of chronic health conditions including obesity. Weight reduction in obese patients lowers the risk for cardiovascular disease, diabetes, certain cancers, and mortality. Achieving a negative energy balance by providing low-calorie meal replacements is widely used for weight management. This study aims to evaluate the impact of a low-calorie “meal-replacement” on the weight and metabolic parameters of shift workers with obesity.

**Methods:**

This trial will be conducted in a parallel, randomized controlled design for a period of 8 weeks. A total of 44 shift workers with body mass index over 25 kg/m^2^ will be recruited after assessing eligibility. Participants will be randomly assigned to the test and control groups on a 1:1 ratio. The intervention group (*N* = 22) will be provided with a low-calorie (~200 kcal) meal replacement shake as dinner, and the control group (*N* = 22) will continue their habitual diets. The visits and the evaluations will be done as follows: screening (visit 0), 4 weeks (visit 1), and 8 weeks (visit 2). Anthropometric measurements will be taken at 0, 4, and 8 weeks. Body composition, biochemical parameters, dietary intake, and physical activity will be assessed during the first and the last visit.

**Outcomes:**

The primary outcome will be the proportion of participants that had a 5% body weight loss from baseline. The secondary outcomes will be post-intervention changes in other metabolic parameters.

**Discussion:**

To our knowledge, this is one of the first randomized controlled trials evaluating the effects of a meal replacement as the night meal for weight loss in shift workers with obesity. Moreover, improvement of metabolic parameters in shift workers will be an added benefit to this high-risk group.

**Trial registration:**

Australian New Zealand Clinical Trials Registry (ANZCTR) ACTRN12622000231741. Registered on 09 February 2022.

**Supplementary Information:**

The online version contains supplementary material available at 10.1186/s13063-022-06784-x.

## Introduction

The prevalence of shift work is increasing in modern society to cater to the complexity and flexibility of many operations that exceed the duration of a normal workday. Shift work is defined as work performed mostly outside of typical working hours [1]. It has been considered a major occupational hazard, and there is a plethora of research showing associations between shift work and chronic diseases [2]. Recent studies have shown that shift work was linked to an elevated risk of obesity, particularly abdominal obesity, with the risk being higher among long-term night shift workers [3].

Obesity is a major contributor to and a risk factor for increased morbidity and mortality due to a variety of diseases [4]. The global obesity burden has doubled since 1980 and the World Health Organization (WHO) predicts that one out of every five persons will be obese by 2025 [5]. Obesity has increased significantly in all South Asian countries [6]. The prevalence of overweight and obesity has increased by almost 40% from 1990 to 2013 in the Southeast Asian region [7]. The level of obesity in Sri Lanka has increased by several folds during the last two decades. According to the Sri Lankan body mass index cut-off (BMI ≥ 25 kg/m^2^), the prevalence of obesity in 2011 was 21.0% and 32.5% in men and women respectively [8]. In 2011, the obesity rate has been increased to 44.6% in males and 56.3% in females [9].

Unhealthy dietary habits, low physical activity, sleep deprivation, and disruption of the circadian rhythm have been proposed as the potential causes underlying weight gain among shift workers [10]. The sleep-wake cycle, thermogenesis, food intake, and lipids and glucose metabolism are reported to be influenced by circadian regulation [1]. Short sleep duration has been shown to lower leptin levels while increasing ghrelin levels, leading to an increase in appetite and weight gain [11]. In support of this view, several studies have shown that night shifts are associated with higher energy intake [12].

In addition, altered food habits also have a profound impact on peripheral circadian clock mechanisms [13]. Shift workers were found to consume more inflammatory diets than day workers, especially for dinner which creates a significant metabolic strain on the body (28). Shift work and snacking during evening work, in particular, are reported as common, with frequent sugar intake in the form of biscuits, soft drinks, and sandwiches that are easy to obtain [14]. Therefore, raising awareness about the effects of shift work on unhealthy food habits, and prescribing evidence-based interventions, may help shift workers’ health by preventing weight gain and associated metabolic consequences [15].

A loss of 5–10% of initial body weight is known to be effective in the treatment of many of the complications associated with obesity such as type 2 diabetes, hypertension, and hyperlipidemia [16]. Weight reduction is associated with increased performance and work capacity in obese individuals, thus contributing towards improving their quality of life [17]. Furthermore, following involvement in weight loss interventions, consistent significant increases in psychological indices such as self-esteem, depressive symptoms, body image, and health-related quality of life have been reported [18].

In comparison to standard energy-deficit diets that simply prescribe a reduction in energy intake, evidence shows that meal replacement diets result in greater weight loss [19], and better compliance [20] is more likely to provide an appropriate intake of essential nutrients, and have higher satisfaction and lower drop-out rates [21]. To the best of our knowledge, dietary intervention with a low-calorie meal replacement meal aimed to lose body weight and improve metabolic parameters has not been tested among night shift workers. Therefore, the present randomized controlled trial will be conducted to investigate the effectiveness of a low-calorie meal replacement dinner compared to a traditional dinner meal on metabolic parameters of shift workers with obesity.

## Methods

This protocol was written following the Standard Protocol Items: Recommendations for Interventional Trials (SPIRIT) checklist (Additional file 1) [22]. The schedule of trial enrollment, interventions, and assessments is presented in Table 1.

**Table 1 Tab1:** Summarized study schedule at each visit in the clinical trial

	Study period			
	Enrolment	Allocation	Post-allocation	
**Time point**	−t_1_ (2 weeks)	0	Visit 1 (4 weeks)	Visit 2 (8 weeks)
**Enrolment**				
Eligibility screening	**×**			
Informed consent	**×**			
Allocation		**×**		
**Interventions**				
Meal replacement group			**×**	**×**
No meal replacement group			**×**	**×**
**Assessments**				
FBG		**×**		**×**
Serum HbA1c		**×**		**×**
Lipid profile		**×**		**×**
Blood pressure		**×**		**×**
Anthropometric measures		**×**	**×**	**×**
Body composition measures		**×**		**×**
FFQ/IPAQ		**×**		**×**

### Objectives and hypothesis

Hypothesis:Primary—prescribing a reduced caloric meal replacement at dinner will have beneficial effects on weight loss of night shift workers with obesity.Secondary—associated metabolic parameters (lipid profile, glycemic outcomes, and blood pressure) will be improved in the treatment group in comparison to the control group.

Objectives:Primary—to investigate if dinner meal replacement with a low-calorie meal replacement shake is an effective strategy to achieve a minimum 5% body weight loss in shift workers with obesity compared to conventional dinnerSecondary—to evaluate the effects on anthropometric parameters, serum lipids, glycemic outcomes, and blood pressure

### Study design and setting

This study will be conducted as a parallel, randomized controlled clinical trial at the Nawaloka Hospital PLC, Colombo, Sri Lanka, for a period of 8 weeks, evaluating the effect of a meal replacement for dinner in obese shift workers.

### Sample size

A sample of 44 healthcare employees who engage in shift work will be recruited for the study after screening for eligibility against the inclusion and exclusion criteria mentioned below. The minimum sample size will be calculated based on the primary outcome, the proportion of participants achieving 5% weight loss after 8 weeks. Previous weight loss intervention trials predicted that 50% of individuals in the intervention group and 10% of participants in the control group would lose at least 5% of their baseline body weight after 8 weeks [23].. To detect this difference in the proportion of participants achieving 5% weight loss between the intervention and control groups, 17 participants were required in each group, to ensure 80% power at a 5% significance level. To accommodate a 20% dropout rate, we, therefore, needed to recruit 22 participants in each intervention group. Hence, a total of 44 adults with obesity (BMI >25 kg/m^2^) will be recruited for the study [24]. The formula used for sample size calculation is presented below:$${n}_B=\left(\frac{P_{\textrm{A}}\left(1-{P}_{\textrm{A}}\right)}{K}+{P}_{\textrm{B}}\left(1-{P}_{\textrm{B}}\right)\right){\left(\frac{Z_{1-\alpha /2}+{Z}_{1-\beta }}{P_{\textrm{A}}-{P}_{\textrm{B}}}\right)}^2$$

*n*
_B_ = Sample size in one arm

*P*
_A_ = Proportion of subjects expected to achieve 5% weight loss at the end of 8 weeks in the placebo group (0.1)

*P*
_B_ = Proportion of subjects expected to achieve 5% weight loss at the end of 8 weeks in the treatment group (0.5)

*Κ* = Sampling ratio (1:1)

*Z*
_α_ = Critical value of the normal distribution at *α* (*α* is 0.05 and the critical value is 1.96)

*Z*
_β_ = Critical value of the normal distribution at *β* (*β* is 0.2)

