### Primary outcome

The primary outcome will be the proportion of participants that had a 5% body weight loss from baseline.

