### Statistical analysis

Using SPSS version 23 (SPSS Inc., Chicago, IL, USA), parametric and non-parametric statistical tests will be applied for data analysis. Summary statistics of each group will be computed and presented as mean, standard deviation, and proportion. Distributions of continuous variables will be tested for normality using the Kolmogorov-Smirnov test. The non-parametric Mann-Whitney *U* test will be used for asymmetrical continuous variables. Using the paired *t*-test, the baseline and end of study characteristics, as well as the laboratory results of the groups, will be compared and a *P* value of <0.05 will be considered significant. The independent sample *t*-tests will be used (or suitable non-parametric test depending on data distribution) for the between-group differences and generalized linear mixed effects models for the analysis of longitudinal data.

Results will be presented as per-protocol and intention-to-treat analysis groups. The analysis will be carried out using the intention-to-treat (ITT) principle where patients’ data will be analyzed as members of the group they were randomized to, irrespective of their compliance with the treatment as specified in the protocol. A per-protocol (PP) analysis will be carried out including all patients who strictly adhere to the protocol in terms of following the treatment, availability of measurements, and absence of major protocol deviations. ITT analysis will use a generalized linear mixed model which can inherently deal with data missing at random. An effort will be made to reduce missing data to a minimum.

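### The stated 80% power at 17 evaluable participants per group rests on an optimistic approximation; exact power for 50% vs 10% is about 63% to 79%, depending on the test

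*Protocol article*

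**What the plan says.** The protocol article, under Primary outcome, defines a binary endpoint: "The primary outcome will be the proportion of participants that had a 5% body weight loss from baseline". For this 8-week endpoint, the planning assumption in the Sample size section reads: "50% of individuals in the intervention group and 10% of participants in the control group would lose at least 5% of their baseline body weight". It concludes that "17 participants were required in each group, to ensure 80% power at a 5% significance level", and then: "To accommodate a 20% dropout rate, we, therefore, needed to recruit 22 participants in each intervention group".

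The section prints its formula, which uses the unpooled variance of a difference in proportions and no small-sample correction. It is two-sided: α "is 0.05 and the critical value is 1.96". Allocation is 1:1.

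The Statistical analysis section lists t-tests, the Mann-Whitney test and generalized linear mixed models. It names no test of two proportions. On missing data it says: "ITT analysis will use a generalized linear mixed model which can inherently deal with data missing at random".

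**The concern.** The 80% is stated without qualification and attached to 17 evaluable participants per group. The formula behind it is a large-sample one. With 17 controls and a 10% rate, the expected number of control responders is 17 × 0.10 = 1.7. In that range the normal approximation to a difference in proportions is unreliable, so the power that the formula promises may not be the power that a test delivers at the 5% level.

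Power is the figure by which a null result will be judged. If the trial finds no difference, readers will take the chance of having missed the assumed effect to be 20%. If the true chance is larger, they will read more into the null result than it can bear.

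**Working it through.** **Inputs (Sample size section).** Control proportion pA = 0.10; intervention proportion pB = 0.50; two-sided α = 0.05 (z = 1.96); power 80% (z = 0.8416); 1:1 allocation; 17 evaluable per arm; 20% dropout; 22 recruited per arm.

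**1. The plan's own figures.** The printed formula gives

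n = [0.10 × 0.90 + 0.50 × 0.50] × [(1.96 + 0.8416)/0.40]² = 0.34 × 49.06 = 16.68, rounded up to 17.

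The same approximation at n = 17 gives a power of Φ(0.40/√(0.34/17) − 1.96) = Φ(2.828 − 1.96) = Φ(0.868) = 80.7%.

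Dropout: 17/0.80 = 21.25, rounded up to 22. Both figures reproduce.

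**2. A sign that the approximation matters.** The pooled-variance version of the formula, with mean proportion 0.30, gives

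n = [1.96 × √(2 × 0.30 × 0.70) + 0.8416 × √0.34]² / 0.40² = (1.270 + 0.491)² / 0.16 = 19.4, rounded up to 20.

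With a continuity correction it gives 25. Three textbook formulas therefore return 17, 20 and 25 for the same inputs.

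**3. Exact power.** For each test, all 18 × 18 possible outcomes at 17 per arm were enumerated. Power is the sum of Bin(17, 0.10) × Bin(17, 0.50) probabilities over the outcomes that the test rejects at nominal two-sided 5%. Maximum size is the largest rejection probability over a common response rate in both arms.

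| Test, 17 per arm | Power | Maximum size | Chance of missing the effect |
|---|---|---|---|
| Fisher exact | 62.6% | 2.4% | 37% |
| Boschloo | 71.5% | 4.3% | 28% |
| Pearson chi-square | 75.0% | 5.8% | 25% |
| Unpooled Wald z (implied by the formula) | 79.2% | 6.1% | 21% |

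None of the four gives 80% power at a 5% level. The two that hold 5% give 63% and 72%.

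**4. Evaluable number needed for at least 80%.**

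| Test | Power just below | Smallest n with at least 80% | With 20% dropout |
|---|---|---|---|
| Pearson | 78.5% at 18 | 19 (81.5%) | 19/0.80 = 23.75, so 24 |
| Boschloo | 79.7% at 19 | 20 (82.2%) | 20/0.80 = 25 |
| Fisher | 78.6% at 22 | 23 (81.1%) | 23/0.80 = 28.75, so 29 |

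The plan recruits 22 per arm.

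**5. Full retention.** With all 22 per arm evaluable, power is 78.6% (Fisher), 86.4% (Boschloo) and 86.4% (Pearson).

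**The case against.** **The formula and its inputs are printed and return 17 and 22.** This stands. A reader might infer an arithmetic slip; there is none. The weakness is the choice of a large-sample approximation where few responders are expected.

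**The size of the shortfall depends on a test that the protocol does not name.** This also stands. The gap runs from about 1 point (Wald) to 17 points (Fisher), and Fisher is the most conservative choice, with a true maximum size of only 2.4%. The choice may be made in an analysis plan that is not shown, so no single power figure can be held against the document. But all four tests fall below 80% at 17 per arm, so the open choice does not rescue the statement.

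**Pearson and Wald cannot be separated by calling one valid.** Correct. Their maximum sizes are 5.8% and 6.1%, and at a common rate of 10% both have a size of 3.1%. A reader who tolerates a slight excess over 5% may count Wald's 79% as roughly the stated 80%. A reader who requires strict control must drop both, which leaves 63% to 72%.

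**The trial recruits 22 per arm, and 20% loss leaves 17.6, not 17.** At 18 per arm, power is 66.8% (Fisher), 78.0% (Boschloo), 78.5% (Pearson) and 81.9% (Wald, maximum size 6.6%). Apart from Fisher, the gap at expected retention is then about 2 points, which is small beside the uncertainty in the 50% and 10% themselves. The protocol nevertheless attaches its 80% to 17.

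**Dilution under intention to treat.** Because participants are to be "analyzed as members of the group they were randomized to, irrespective of their compliance with the treatment", a reader might infer that dropouts count as non-responders, so that both proportions shrink and power falls further. The documents do not support this. They state no non-responder rule, and they plan a mixed model for data missing at random. Inflating the sample for dropout is ordinary with such an analysis.

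**Conclusion.** The concern holds as a matter of approximation. Under the plan's own assumptions, 17 evaluable per arm does not deliver 80% power at a two-sided 5% level with any of the four tests examined. The shortfall is 8 to 17 points for the tests that hold 5% (Boschloo, Fisher), 5 points for Pearson, and about 1 point for the Wald test that the formula implies; the last two slightly exceed 5% in the worst case.

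This rests on true proportions of 50% and 10%, an unadjusted comparison of two proportions, and 17 evaluable per arm. It does not mean that the trial is underpowered at every level of retention: with all 22 per arm evaluable, Boschloo and Pearson exceed 80% and Fisher comes close. The generalized linear mixed model was not evaluated here, because its form for the binary outcome is not given.

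**What to change.** Keep N = 44. In the Sample size section, name the test of the two proportions for the primary outcome, and state its exact power at 17 and at 22 evaluable per arm. Boschloo's test is one suitable choice: at 17 per arm it gains about 9 points over Fisher (71.5% against 62.6%) while holding 5%. The text could then say that, for 50% vs 10% at two-sided 5%, power by Boschloo's test is about 72% with 17 evaluable per arm and 86% with 22. If another test is preferred, its own pair of figures should be given: 63% and 79% for Fisher; 75% and 86% for Pearson, with a note that its maximum size is 5.8% at 17 per arm and 5.2% at 22.

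The cost is a change of wording. No participants are added and no procedure changes. The downside is that the stated power becomes less favourable. The Trial status section says that enrolment has not started, so on the document's own account the change can precede any data.

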### Population

The study population will consist of obese healthcare employees in rotating shift work who provides health care services, either directly (e.g., doctors and nurses) or indirectly (e.g., helpers, laboratory technicians, medical waste handlers, security officers).

### Inclusion and exclusion criteria

#### Inclusion criteria

Permanent employees aged 18–65 yearsHave been working shifts continuously for the past 12 months and continue during the whole study period (8 weeks).Working at least 3 night shifts/weekParticipants with BMI ≥25 kg/m^2^Not having any allergies to any of the known food ingredients, especially for milk and soya

#### Exclusion criteria

Pregnant or lactating mothersHaving known chronic disease conditionsHaving a known allergy history for milk or any of the ingredients in the meal replacement.History of any type of minor or major surgical procedure in the past 6 months.Currently on diet prescriptions or participating in regular physical activity sessions

#### Criteria for discontinuing or modifying the allocated intervention

Subject’s request to discontinue the studySerious adverse events or unusual changes in clinical test resultsPrincipal investigator’s decision to terminate the study (low compliance rate, complications, or unable to continue the study due to various reasons)

There are no criteria for modifying allocated intervention.

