#### Study schedule

Anthropometric measures, blood pressure, fasting plasma glucose, serum HbA1c, and lipid profile will be measured at the time of recruitment of participants and will be repeated at the end of the 8th week. However, anthropometry measures will be again measured at the end of the 4th week additionally. The details of items that will be measured at every visit are described in Table 1.

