#### Compliance calculation

Powdered meal replacement will be dispensed to each participant at baseline, end of the 2nd, 4th, and 6th weeks. Participants will be instructed to return any unused meal replacement powder to the investigator at the end of the study. Compliance will be evaluated using the following formula:$$\textrm{Compliance}\%=\frac{\left(\textrm{Distributed}\ \textrm{meal}\ \textrm{replacement}\ \textrm{quantity}-\textrm{Remaining}\ \textrm{meal}\ \textrm{replacement}\ \textrm{quantity}\right)}{\textrm{Distributed}\ \textrm{meal}\ \textrm{replacement}\ \textrm{quantity}}\times 100$$

In addition, researchers will phone participants periodically to monitor the consumption of the meal replacement. Each participant will be asked to record the meal replacement intake each day in a compliance assessment sheet provided at baseline. At each visit, these consumption records will be cross-checked with subjects. WhatsApp® groups will be created for communication with intervention and control groups.

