### Data collection

Data collection will be performed according to the standard operating procedures (SOPs) by the principal investigator and trained research assistants. The principal investigator will be responsible for establishing and maintaining contact with participants throughout the study. Contact information will be collected at enrollment, including alternate phone numbers and a contact person who will always be aware of the participant’s activities. The study coordinator will follow up with a call to reschedule if study appointments are missed.

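### Letting the investigator end study participation for low compliance could cost week-8 weights mainly in the shake arm; the rule should stop the shake, not the follow-up

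*Protocol article*

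**What the plan says.** The section on criteria for discontinuing or modifying the allocated intervention has three items: the subject's own request, serious adverse events or unusual test results, and the principal investigator's "decision to terminate the study (low compliance rate, complications, or unable to continue the study due to various reasons". It sets no compliance threshold. Although the heading concerns the intervention, the first and third items speak of leaving or ending the study.

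The section on compliance calculation defines compliance from shake powder distributed and remaining. Participants are to "return any unused meal replacement powder to the investigator at the end of the study". Before then, monitoring rests on periodic phone calls and on asking each participant to "record the meal replacement intake each day in a compliance assessment sheet", with the records cross-checked at visits.

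Under Statistical analysis, participants are to be "analyzed as members of the group they were randomized to, irrespective of their compliance with the treatment". Adherence enters only through the per-protocol set, "including all patients who strictly adhere to the protocol in terms of following the treatment". On missing data the article says "ITT analysis will use a generalized linear mixed model which can inherently deal with data missing at random", and it adds a general commitment to keep missing data low.

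Under Data collection, "The study coordinator will follow up with a call to reschedule if study appointments are missed". Under Study schedule, "anthropometry measures will be again measured at the end of the 4th week additionally", so weight is due at baseline, week 4 and week 8.

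**The concern.** The discontinuation rule does not separate stopping the shake from leaving the trial. If a low complier is taken out of the study and not weighed at week 8, that person's primary outcome is missing. Low compliers are probably less likely to lose 5% of body weight, so such losses would be related to outcome. With no compliance measure for the usual-dinner arm, they would also fall mainly on one side. The remaining shake arm would then look more successful than the randomized arm, and per-protocol selection would have entered the intention-to-treat data. What is at stake is the estimated response rate, and hence the estimated difference, for the primary outcome.

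**Working it through.** **1. Which level does the rule act on?** Three readings are open: stop the shake, remove the individual, or stop the whole trial. The neighbouring item is one subject's request. Whole-trial termination has its own rule under Adverse effect evaluation, on safety grounds, where low compliance is not listed. Participant level is therefore the natural reading. Only removal of the individual without further weighing does harm.

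**2. Which arm?** The compliance formula, calls and intake sheets all concern the shake. Controls eat their usual dinner. The rule therefore bears mainly on the shake arm.

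**3. When?** The compliance percentage needs powder returned at the end of the study, so an earlier decision would rest on calls and self-completed sheets. The sheets are cross-checked at visits, and the first visit after baseline is at week 4.

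**4. The plan's own figures, for scale.** Under Sample size, the assumed rates are 0.5 (shake) and 0.1 (control), with 80% power, 5% significance and 20% dropout:

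(0.1×0.9 + 0.5×0.5) × ((1.96 + 0.8416)/0.4)² = 16.68, rounded up to 17; 17/0.8 = 21.25, rounded up to 22 per arm.

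Both stated figures reproduce, and nothing here disputes them. The allowance is 22 − 17 = 5 losses per arm.

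**5. Illustration, removal before week 4.** Assumed, not in the documents: true shake-arm rate 50% (11/22), k people removed and unweighed, and a response rate q among them. These people have no post-baseline weight for the mixed model to use, so the estimate is close to the rate among those weighed, (11 − kq)/(22 − k):

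| k | q = 0 | q = 0.10 | q = 0.50 |
|---|---|---|---|
| 1 | 11/21 = 52.4% | 10.9/21 = 51.9% | 50% |
| 2 | 11/20 = 55.0% | 10.8/20 = 54.0% | 50% |
| 3 | 11/19 = 57.9% | 10.7/19 = 56.3% | 50% |
| 4 | 11/18 = 61.1% | 10.6/18 = 58.9% | 50% |
| 5 | 11/17 = 64.7% | 10.5/17 = 61.8% | 50% |

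If the true rate were only 10% (2.2/22), the worst case shown (k = 5, q = 0) gives 2.2/17 = 12.9%, or 2.9 points too high.

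**6. Illustration, removal after week 4.** Here week-4 weight can help. A simulation (2 million per setting) kept the true rate at 50%. It assumed a standard deviation of percentage weight loss of 2 at week 4 and 3 at week 8, a week-4 mean equal to 55% of the week-8 mean, and a within-person correlation of 0.50 to 0.85. Missing week-8 losses were predicted from week-4 loss by the regression in completers.

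- Lowest week-4 losses removed: 49.9% to 50.1%, so no bias.
- Removal depending on week-8 responder status, q = 0 to 0.10: 53.8% to 58.6% with 4 removed, 54.9% to 61.2% with 5.
- Lowest week-8 losses removed: 52.4% to 59.4% with 4 removed, 53.9% to 62.8% with 5.

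The recovery assumes that continuous week-4 weight is used in the model.

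**7. Effect on the test.** Fisher's exact test, two-sided, with an assumed control result of 2/22: 11/22 v 2/22 gives p = 0.0068; 11/17 v 2/22 gives p = 0.0004. Both are significant, so the estimate moves and the conclusion does not.

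**The case against.** A reader might infer that the protocol orders low compliers out and stops weighing them, and so contradicts its own intention-to-treat rule. The documents do not support that. The heading concerns the intervention, and no section ends measurement for those who stop. The intention-to-treat text expects low compliers in the data, plans a model for missing values and commits to limiting them. The principal investigator is to keep contact with participants throughout, and the call about missed appointments carries no exception for people the investigator has stopped. All of this stands, and it reduces the point from a contradiction to a risk that the wording leaves open.

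It can also be said that a condensed article need not describe follow-up after discontinuation. That has less force here, because the point turns on what the stated rule permits, and the article describes itself as giving the full protocol.

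Two further objections stand in part. One-sidedness is inferred: a control participant could be stopped under the residual clause, for example for using a prohibited weight-loss treatment, so the effect is mainly, not exclusively, in the shake arm. The largest figures also need removal before week 4, although records are first cross-checked at week 4, when weight is taken. Earlier removal would have to follow a phone call or the week-2 dispensing contact, so the 65% case is an unlikely extreme.

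Finally, a reader might infer that a positive result could be an artefact. The calculations do not show that: significance at the planned rates is unchanged, and at a true rate of 10% the shift is at most 2.9 points within the range examined.

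**Conclusion.** The concern holds as a minor weakness of wording. A discretionary rule without a threshold can take low compliers out of the study, it would act mainly in the shake arm, and nothing stated guarantees that those removed are weighed at week 8. That works against an analysis intended to ignore compliance.

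The documents give neither the number who would be removed nor how they would respond, so no bias can be derived from them. Under the assumed values the shift in the shake-arm rate runs from 0 to about 15 points; the reference case, 4 of 22 non-responders lost before week 4, gives about 11 points (50% to 61%). There is no bias if those removed are still weighed, if they respond like the others, or if removal depends only on a week-4 weight that the model uses.

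**What to change.** Reword the third discontinuation criterion so that low compliance may stop the shake but not study participation. Add that all randomized participants are weighed at weeks 4 and 8 unless they withdraw consent, that they stay in the intention-to-treat analysis, and that low compliance affects only membership of the per-protocol set. Leave termination of the whole trial to the safety rule under Adverse effect evaluation.

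The cost is a few sentences before enrolment, which the article says has not started, and a few more weighings at visits already scheduled. No sample size or other figure changes. This is a cheap improvement of minor severity.
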